## **6.7. Packaging**

See Appendix G.

## **6.8. Vaccine accountability**

See Appendix G.

## **6.9. Concomitant medication/treatment**

At each study visit/contact, the investigator should question the enrolled subject's parent(s)/guardian(s) about any medication(s) taken.

All antipyretic, analgesic and antibiotic drugs, administered at ANY time during the period starting with administration of each dose and ending 30 days after each dose of vaccine are to be recorded with generic name of the medication (trade names are allowed for combination drugs, i.e., multi-component drugs), medical indication, total daily dose, route of administration, start and end dates of treatment.

Any treatments and/or medications which are listed as elimination criteria in Section 4.8, e.g., any immunoglobulins, other blood products and any immune modifying drugs administered within three months preceding the first dose or at any time during the study period are to be recorded with generic name of the medication (trade names are allowed for combination drugs only), medical indication, total daily dose, route of administration, start and end dates of treatment. Refer to Sections 4.7 to 4.9. The time periods between which each type of concomitant medication/treatment should be recorded is summarized in Table 8.

**Table 8            Summary of time periods between which different classes of concomitant medication/treatment/vaccination must be recorded**

|                                                |                                                                                                                              |
|------------------------------------------------|------------------------------------------------------------------------------------------------------------------------------|
| 3 months prior to Dose 1 → Dose 1       | All treatments listed as elimination criteria in Section 4.8*                                                                |
| Screening → 30 Days post Dose 3         | All antipyretic, analgesic, antibiotic and any treatments listed as elimination criteria in Section 4.8*
All vaccinations |
| 31 Days post Dose 3 → Final Study Visit | All treatments listed as elimination criteria in Section 4.8*                                                                |

\* e.g. any immunoglobulins, other blood products and any immune modifying drugs

Any vaccine not foreseen in the study protocol administered in the period beginning 30 days preceding each dose and ending 30 days after each dose is to be recorded with trade name, route of administration and date(s) of administration. Refer to Sections 4.7 to 4.9.

Any concomitant medication administered prophylactically in anticipation of reaction to the vaccination must be recorded in the CRF with generic name of the medication (trade names are allowed for combination drugs only), total daily dose, route of administration, start and end dates of treatment and coded as 'Prophylactic'.

## **7.            HEALTH ECONOMICS**

Not applicable

## **8.            ADVERSE EVENTS AND SERIOUS ADVERSE EVENTS**

The investigator is responsible for the detection and documentation of events meeting the criteria and definition of an adverse event (AE) or serious adverse event (SAE) as provided in this protocol. During the study, when there is a safety evaluation, the investigator or site staff will be responsible for detecting AEs and SAEs, as detailed in this section of the protocol.

Each subject/ subject's parents/guardians will be instructed to contact the investigator immediately should they/ the subject manifest any signs or symptoms they perceive as serious.

## 8.1. Definition of an adverse event

An AE is any untoward medical occurrence in a clinical investigation subject, temporally associated with the use of a medicinal product, whether or not considered related to the medicinal product.

An AE can therefore be any unfavorable and unintended sign (including an abnormal laboratory finding), symptom, or disease (new or exacerbated) temporally associated with the use of a medicinal product.

Examples of an AE include:

- Exacerbation of a chronic or intermittent pre-existing condition including either an increase in frequency and/or intensity of the condition.
- New conditions detected or diagnosed after investigational product administration even though it may have been present prior to the start of the study.
- Signs, symptoms, or the clinical sequelae of a suspected overdose of either investigational product or a concurrent medication (overdose per se should not be reported as an AE/SAE).
- Signs, symptoms temporally associated with vaccine administration.

AEs may include pre- or post-treatment events that occur as a result of protocol-mandated procedures (i.e., invasive procedures, modification of subject's previous therapeutic regimen).

N.B. AEs to be recorded as endpoints (solicited events) are described in Section 8.4.1. All other AEs will be recorded as **UNSOLICITED AEs**.

Example of events to be recorded in the medical history section of the CRF:

- Pre-existing conditions or signs and/or symptoms present in a subject prior to the start of the study (i.e. prior to the first study procedure) should be recorded in the medical history section of the subject's CRF.

## 8.2. Definition of a serious adverse event

A serious adverse event (SAE) is any untoward medical occurrence that:

- a. results in death;
- b. is life-threatening;

*NOTE: The term 'life-threatening' in the definition of 'serious' refers to an event in which the subject was at risk of death at the time of the event. It does not refer to an event, which hypothetically might have caused death, if it were more severe.*

- c. requires hospitalization or prolongation of existing hospitalization;

*NOTE: In general, hospitalization signifies that the subject has been detained (usually involving at least an overnight stay) at the hospital or emergency ward for observation*

*and/or treatment that would not have been appropriate in the physician's office or out-patient setting. Complications that occur during hospitalization are AEs. If a complication prolongs hospitalization or fulfills any other serious criteria, the event is serious. When in doubt as to whether 'hospitalization' occurred or was necessary, the AE should be considered serious.*

*Hospitalization for elective treatment of a pre-existing condition that did not worsen from baseline is not considered an AE.*

- d. results in disability/incapacity;

*NOTE: The term disability means a substantial disruption of a person's ability to conduct normal life functions. This definition is not intended to include experiences of relatively minor medical significance such as uncomplicated headache, nausea, vomiting, diarrhea, influenza, and accidental trauma (e.g. sprained ankle) which may interfere or prevent everyday life functions but do not constitute a substantial disruption.*

- e. medical or scientific judgment should be exercised in deciding whether reporting is appropriate in other situations, such as important medical events that may not be immediately life-threatening or result in death or hospitalization but may jeopardize the subject or may require medical or surgical intervention to prevent one of the other outcomes listed in the above definition. These should also be considered serious. Examples of such events are invasive or malignant cancers, intensive treatment in an emergency room or at home for allergic bronchospasm, blood dyscrasias or convulsions that do not result in hospitalization.

In this study all seizures occurring within a 30-day period of vaccination will be notified as SAEs [refer to Bonhoeffer 2004]. Key information pertaining to seizures will be documented in the CRF.

### **8.3. Clinical laboratory parameters and other abnormal assessments qualifying as adverse events and serious adverse events**

Abnormal laboratory findings (e.g., clinical chemistry, hematology, urinalysis) or other abnormal assessments (e.g. blood film ) that are judged by the investigator to be clinically significant will be recorded as AEs or SAEs if they meet the definition of an AE, as defined in Section 8.1 or SAE, as defined in Section 8.2. Clinically significant abnormal laboratory findings or other abnormal assessments that are detected during the study or are present at baseline and significantly worsen following the start of the study will be reported as AEs or SAEs.

The investigator will exercise his medical and scientific judgment in deciding whether an abnormal laboratory finding or other abnormal assessment is clinically significant.

#### **8.4. Time period, frequency, and method of detecting adverse events and serious adverse events**

All AEs occurring within 30 days following administration of each dose of vaccine must be recorded on the Adverse Event form in the subject's CRF, irrespective of severity or whether or not they are considered vaccination-related.

The standard time period for collecting and recording SAEs will begin at first receipt of vaccine and will end at the study conclusion. See Section 8.7 for instructions for reporting and recording SAEs.

Additionally, in order to fulfill international reporting obligations, SAEs that are related to study participation (e.g. procedures, vaccinations, invasive tests, transport to and from study visits) or are related to a concurrent medication will be collected and recorded from the time the subject consents to participate in the study until she/he is discharged: if a child is screened and enrolled, then discharge will be the end of the study as per study protocol; if a child is screened but not enrolled, then discharge will be the point at which the decision is taken not to enroll the child.

The investigator will inquire about the occurrence of AEs/SAEs at every visit/contact during the study and throughout the follow-up phase as appropriate.

The mechanism by which SAEs will be identified in the study are detailed in Section 5.7. The investigator or study clinician will fully document any such events on the Serious Adverse Event pages appended to the individual Case Report Form including, where applicable, information from relevant hospital case records, autopsy reports and verbal autopsies.

All AEs either observed by the investigator, study clinician, field worker or reported by the subject's parent/guardian spontaneously or in response to a direct question will be evaluated by the investigator. AEs not previously documented in the study will be recorded in the Adverse Event form within the subject's CRF. The nature of each event, date and time (where appropriate) of onset, outcome, intensity and relationship to vaccination will be established. Details of any corrective treatment will be recorded on the appropriate page of the CRF. Refer to Section 6.9.

As a consistent method of determining the occurrence of unsolicited AEs, the subject or the subject's parent/guardian will be asked a non-leading question such as:

‘Has your child acted differently or felt different in any way since receiving the vaccine or since the last visit ‘

N.B. The investigator should record only those AEs having occurred within the time frame defined above.

AEs already documented in the CRF, i.e. at a previous assessment, and designated as ‘not recovered/not resolved’ or ‘recovering/resolving’ should be reviewed at subsequent visits, as necessary. If these have resolved, the documentation in the CRF should be completed.

When an AE/SAE occurs, it is the responsibility of the investigator to review all documentation (e.g., hospital progress notes, laboratory, verbal autopsies and diagnostics reports) relative to the event. The investigator will then record all relevant information regarding an AE/SAE on the CRF or SAE Report Form as applicable. It is not acceptable for the investigator to send photocopies of the subject's medical records to GSK Biologicals in lieu of the appropriate completed AE/SAE pages. However, there may be instances when copies of medical records and verbal autopsies for certain cases are requested by GSK Biologicals. In this instance, all subject identifiers will be blinded on the copies of the medical records prior to submission to GSK Biologicals.

The investigator will attempt to establish a diagnosis of the event based on signs, symptoms, and/or other clinical information. In such cases, the diagnosis should be documented as the AE/SAE and not the individual signs/symptoms.

#### **8.4.1. Solicited adverse events**

##### **Local (injection site) adverse events**

- Pain at injection site
- Swelling at injection site

##### **General adverse events**

- Fever (defined as axillary temperature  $\geq 37.5^{\circ}\text{C}$ )
- Drowsiness
- Loss of appetite
- Irritability/fussiness

The visiting field worker will record these adverse events according to detailed SOPs available on study site during the field worker visits.

**N.B. Temperature will be recorded on days 1 to 6 following each vaccination by the field worker or Principal Investigator (or their delegate). Should additional temperature measurements be performed at other times of day, the highest temperature will be recorded.**

#### **8.5. Evaluating adverse events and serious adverse events**

##### **8.5.1. Assessment of intensity**

Intensity of the following AEs will be assessed as described:

**Table 9 Intensity scales for solicited symptoms in infants/toddlers and children less than 6 years of age**

| Adverse Event              | Intensity grade | Parameter                                                 |
|----------------------------|-----------------|-----------------------------------------------------------|
| Pain at injection site     | 0               | Absent                                                    |
|                            | 1               | Minor reaction to touch                                   |
|                            | 2               | Cries/protests on touch                                   |
|                            | 3               | Cries when limb is moved/spontaneously painful            |
| Swelling at injection site |                 | Record greatest surface diameter in mm                    |
| Fever*                     |                 | Record temperature in °C                                  |
| Irritability/Fussiness     | 0               | Behavior as usual                                         |
|                            | 1               | Crying more than usual/ no effect on normal activity      |
|                            | 2               | Crying more than usual/ interferes with normal activity   |
|                            | 3               | Crying that cannot be comforted/ prevents normal activity |
| Drowsiness                 | 0               | Behavior as usual                                         |
|                            | 1               | Drowsiness easily tolerated                               |
|                            | 2               | Drowsiness that interferes with normal activity           |
|                            | 3               | Drowsiness that prevents normal activity                  |
| Loss of appetite           | 0               | Appetite as usual                                         |
|                            | 1               | Eating less than usual/ no effect on normal activity      |
|                            | 2               | Eating less than usual/ interferes with normal activity   |
|                            | 3               | Not eating at all                                         |

\*Fever is defined as axillary temperature  $\geq 37.5^{\circ}\text{C}$

The maximum intensity of local injection site swelling will be scored at GSK Biologicals as follows:

|   |   |            |
|---|---|------------|
| 0 | : | None       |
| 1 | : | < 5 mm     |
| 2 | : | 5 to 20 mm |
| 3 | : | > 20 mm    |

The maximum intensity of fever will be scored at GSK Biologicals as follows:

|   |   |               |
|---|---|---------------|
| 0 | : | < 37.5°C      |
| 1 | : | 37.5 – 38.0°C |
| 2 | : | > 38 – 39.0°C |
| 3 | : | > 39.0°C      |

**Table 10 Acceptable/normal ranges for blood testing**

|                            | Acceptable limit/
normal range                                    | Toxicity grading scale                 |                                        |                                        |                                                                   |
|----------------------------|----------------------------------------------------------------------|----------------------------------------|----------------------------------------|----------------------------------------|-------------------------------------------------------------------|
|                            |                                                                      | Grade 1                                | Grade 2                                | Grade 3                                | Grade 4                                                           |
| Hemoglobin                 | $\geq 8.0$ g/dL                                                      | < ULN                                  | < 6.0 g/dL                             | < 5.0 g/dL                             | < 5.0 g/dL &
clinical signs of
heart failure                |
| Total white
cell count† | $\geq 4.0 \times 10^3/\mu\text{L}$
$< 17 \times 10^3/\mu\text{L}$ | $2.5$ to $4.0 \times 10^3/\mu\text{L}$ | $1.5$ to $2.4 \times 10^3/\mu\text{L}$ | $1.0$ to $1.4 \times 10^3/\mu\text{L}$ | $< 1.0 \times 10^3/\mu\text{L}$                                   |
| Platelets†                 | $\geq 100 \times 10^3/\mu\text{L}$                                   | $50$ to $99 \times 10^3/\mu\text{L}$   | $25$ to $49 \times 10^3/\mu\text{L}$   | $< 25 \times 10^3/\mu\text{L}$         | $< 25 \times 10^3/\mu\text{L}$
& clinical signs
of bleeding |
| ALT*                       | $\leq 60$ $\mu\text{mol/L}$                                          | $1.1$ to $2.5 \times \text{ULN}$       | $2.6$ to $5.0 \times \text{ULN}$       | $5.1$ to $10.0 \times \text{ULN}$      | $> 10.0 \times \text{ULN}$                                        |
| Creatinine*                | $\leq 60$ $\mu\text{mol/L}$                                          | $1.1$ to $1.5 \times \text{ULN}$       | $1.6$ to $3.0 \times \text{ULN}$       | $3.1$ to $6.0 \times \text{ULN}$       | $> 6.0 \text{ ULN}$ or
requires
dialysis                    |

† Grading scale adapted from Division of AIDS table for grading severity of adult and pediatric adverse events December 2004

\* Grading scale adapted from WHO Toxicity Grading Scale for Determining Severity of Adverse Events, February 2003.

ULN: Upper Limit of Normal

The investigator will make an assessment of the maximum intensity that occurred over the duration of the event for all other AEs, i.e. unsolicited symptoms, including SAEs reported during the study. The assessment will be based on the investigator's clinical judgment. The intensity of each AE and SAE recorded in the CRF or SAE Report Form, as applicable, should be assigned to one of the following categories:

- 1 (mild) = An AE which is easily tolerated by the subject, causing minimal discomfort and not interfering with everyday activities.
- 2 (moderate) = An AE which is sufficiently discomforting to interfere with normal everyday activities.
- 3 (severe) = An AE which prevents normal, everyday activities. (In a young child, such an AE would, for example, prevent attendance at school/ kindergarten/ a day-care center and would cause the parents/ guardians to seek medical advice. In adults/ adolescents, such an AE would, for example, prevent attendance at work/ school and would necessitate the administration of corrective therapy.)

An AE that is assessed as Grade 3 (severe) should not be confused with a SAE. Grade 3 is a category utilized for rating the intensity of an event; and both AEs and SAEs can be assessed as Grade 3. An event is defined as 'serious' when it meets one of the pre-defined outcomes as described in Section 8.2.

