### **4.3. Malaria epidemiology and control in the study area**

Malaria transmission in the study area is intense and there is little seasonal variability in transmission rates or parasite prevalence [Wildling 1995; Sylla 2001]. *Plasmodium falciparum* is the predominant species and responsible for 95% of all infections. The main vectors are *Anopheles gambiae* and *An. moucheti*. The entomological inoculation rate lies around 50 infective bites per person per year [Sylla 2000].

The level of chloroquine resistance is high, reaching 100% both in vitro and in vivo [Borrmann 2002]. Resistance of local parasite strains to sulfadoxine/pyrimethamine is moderate and rising steadily. A recent study in Lambaréné found a treatment failure of 21% in children on Day 14 [Allouche 2004]. The policy of the government of Gabon is to treat all children with malaria with Artemisinin-based Combination Therapy (ACT).

On average, children aged 2 to 12 years experience about 1.5 malarial attacks per year, with large variability among individuals [[name] 1999]. Anemia is common: around 70% of children tested at HAS MRU have Hb < 9g/dL; about 17% of children have Hb < 5g/dL [[name] unpublished].

There is no widely implemented national or local bednet programme. Although part of the population sleep under bednets, these are rarely impregnated, installed properly or well-maintained.

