#### **4.7. Exclusion criteria for enrolment**

The following criteria should be checked at the time of study entry. If any apply, the subject must not be included in the study:

- Acute disease at the time of enrolment (acute disease is defined as the presence of a moderate or severe illness with or without fever). All vaccines can be administered to persons with a minor illness, such as diarrhea or mild upper respiratory infection without fever, i.e. axillary temperature < 37.5°C.

- Serious acute or chronic illness determined by clinical or physical examination and laboratory screening tests including, but not limited to:
  - Any confirmed or suspected immunosuppressive or immunodeficient condition, based on medical history and physical examination (no laboratory testing required)
  - A family history of congenital or hereditary immunodeficiency
  - History of splenectomy
  - Major congenital defects
  - History of any neurologic disorders or seizures
  - Moderate malnutrition at screening defined as weight for age Z-score less than -2.
- Laboratory screening tests out of range, specifically:
  - refer to Table 10
- Planned administration/administration of a vaccine not foreseen by the study protocol within 30 days of the first dose of vaccine(s) with the exception of tetanus toxoid.
- Use of any investigational or non-registered drug or vaccine within 30 days preceding the first dose of study vaccine, or planned use during the study period.
- Administration of immunoglobulins, blood transfusions or other blood products within the three months preceding the first dose of study vaccine or planned administration during the study period.
- Chronic administration (defined as more than 14 days) of immunosuppressants or other immune-modifying drugs within six months prior to the first vaccine dose (for corticosteroids, this will mean prednisone, or equivalent,  $\geq 0.5$  mg/kg/day. Inhaled and topical steroids are allowed).
- Previous participation in any other malaria vaccine trial.
- Simultaneous participation in any other clinical trial.
- Same sex twin.
- History of allergic reactions (significant IgE-mediated events) or anaphylaxis to previous immunizations.
- History of allergic disease or reactions likely to be exacerbated by any component of the vaccine.
- Any other findings that the investigator feels would increase the risk of having an adverse outcome from participation in the trial.

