#### **5.1.3.3. Safety monitoring reports**

Safety reports will be produced for the DSMB on all data collected until two points in the study; after 40 subjects have been enrolled and have completed the first 7 days of follow-up post Dose 1 and after 40 subjects have completed the first 7 days of follow-up post Dose 2. An independent statistician will analyze the data and prepare an unblinded report for the DSMB thereby maintaining the blind of the malaria project team at GSK Biologicals and the investigator group. If a criterion for the suspension of progression to the next sequential vaccine dose is met, or the DSMB have any safety concerns about the vaccines, they may suspend the progression to the next vaccine dose. The process outlined in Section 5.1.3.4 will be followed.

The reports will contain for the first 40 children to receive each sequential vaccine dose:

- All SAEs and any relationship to vaccine (RTS,S/AS02D or RTS,S/AS01E) to date;
- For each of the first two doses (i.e. after Dose 1 and Dose 2) of RTS,S/AS02D and RTS,S/AS01E, all solicited AEs tabulated by severity grading (any and Grade 3 alone – refer to Table 9) and relationship to vaccine;
  - Should the investigator judge a case of Grade 3 fever to be unrelated to vaccination, an alternative explanation for the cause of the fever will be provided
- For each of the first two doses (i.e. after Dose 1 and Dose 2) of RTS,S/AS02D and RTS,S/AS01E, all unsolicited AEs tabulated by severity grading (any and Grade 3 alone – refer to Table 9) and relationship to vaccine;

- All laboratory values up to 30 days post Dose 2 presented as number of subjects out of range (above and below normal range) at each sampling time point (post doses 1 and 2 of RTS,S/AS02D or RTS,S/AS01E) tabulated by toxicity grading scale (refer to Table 10);
  - For all subjects with toxicity grading scale  $\geq 3$ , full clinical details will be provided
- All withdrawals of study subjects by the Principal Investigator due to adverse events recorded from the children or withdrawals of children by the parent(s)/guardian(s) following doses of RTS,S/AS02D or RTS,S/AS01E (expressed as percentage of subjects enrolled).

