## **5.6. Monitoring of hematological and biochemical laboratory parameters**

Blood for safety monitoring of hematology, renal and hepatic function will be measured at screening, one week post Dose 1, one month post Dose 3 and 12 months post Dose 3. The hematological and biochemical parameters will be documented on the CRF. For all values outside the normal range (refer to Table 10), the reason and/or clinical condition will be documented. Results of hematological and biochemical laboratory tests will be reviewed as soon as they are generated. Any value outside the normal range will be managed as appropriate by a medically qualified individual under the supervision of the Principal Investigator (refer to Section 8.6). Guidance on when to report abnormalities as SAEs is given in Section 8.3.

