## **8.6. Follow-up of adverse events and serious adverse events and assessment of outcome**

After the initial AE/SAE report, the investigator is required to proactively follow each subject and provide further information to GSK Biologicals on the subject's condition.

All AEs and SAEs documented at a previous visit/contact and designated as not recovered/not resolved or recovering/resolving will be reviewed at subsequent visits/contacts.

Investigators will follow-up subjects:

- with SAEs or subjects withdrawn from the study as a result of an AE, until the event has resolved, subsided, stabilized, disappeared, the event is otherwise explained, or the subject is lost to follow-up;
- or, in the case of other non-serious AEs, until they complete the study or they are lost to follow-up.

All Grade 3, Grade 4 or clinically significant laboratory abnormalities will be followed up until they have returned to normal, or a satisfactory explanation has been provided. Additional information (including but not limited to laboratory results) relative to the subsequent course of such an abnormality noted for any subject must be made available to the Study Monitor.

GSK Biologicals may request that the investigator perform or arrange for the conduct of supplemental measurements and/or evaluations to elucidate as fully as possible the nature and/or causality of the AE or SAE. The investigator is obliged to assist. If a subject dies during participation in the study or during a recognized follow-up period, GSK Biologicals will be provided with a copy of any available post-mortem findings, including histopathology.

New or updated information will be recorded on the originally completed SAE Report Form, with all changes signed and dated by the investigator. The updated SAE report form should be resent to GSK Biologicals within 24 hours of receipt of the follow-up information as outlined in Section 8.7.1.

Outcome of any non-serious AE occurring within 30 days post-vaccination (i.e. unsolicited AE) or any SAE reported during the entire study will be assessed as:

- Recovered/resolved
- Not recovered/not resolved
- Recovering/resolving
- Recovered with sequelae/resolved with sequelae

- Fatal (SAEs only).

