#### **10.8.1.2. Secondary safety endpoints**

Safety will be analyzed on the Total Cohort.

The percentage of subjects with at least one local adverse event (solicited and unsolicited), with at least one general adverse event (solicited and unsolicited) and with any adverse event during the solicited follow-up period will be tabulated with exact 95% CI after each vaccine dose and overall. The percentage of doses followed by at least one local adverse event (solicited and unsolicited), by at least one general adverse event (solicited and unsolicited) and by any adverse event will be tabulated, overall vaccination course, with exact 95% CI. Similar tables will be generated for Grade 3 events, the relationship of the event to vaccination.

The percentage of subjects reporting each individual solicited local and general adverse event during the solicited follow-up period will be tabulated with exact 95% CI. The percentage of doses followed by each individual solicited local and general adverse event will be tabulated, overall vaccination course, with exact 95% CI. Similar tables will be generated for Grade 3 events, the relationship of the event to vaccination and for fever, temperature (in 0.5°C increments).

The proportion of subjects reporting an AE (unsolicited) 30 days post each vaccination, classified by the MedDRA preferred term level, reported from study start until the end of the double-blind phase (visit 6) will be tabulated with exact 95% CI.

Biochemistry (ALT, bilirubin, creatinine) and hematology (hemoglobin, WBC, platelets) values that are outside of the reference ranges will be described for Clinic Visit 6 (end of double-blind phase). Frequency distribution of results by toxicity grades will be tabulated by group.

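### Table 10 grades acceptable hemoglobin (8.0 g/dL up to the ULN) and a white-cell count of exactly 4.0 as Grade 1, so Grade 1 counts mix acceptable and low values

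*Protocol*

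**What the plan says.** Table 10 (protocol Section 8.5.1) has one column for the acceptable limit or normal range and four columns of toxicity grades. The rows that matter here are:

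- **Hemoglobin:** acceptable at 8.0 g/dL or more; Grade 1 below ULN; Grade 2 below 6.0; Grade 3 below 5.0; Grade 4 below 5.0 with clinical signs of heart failure.
- **White cells (× 10³/µL):** acceptable from 4.0 to below 17. The Grade 1 cell is printed as "2.5$ to $4.0 \times 10^3/\mu\text{L", that is, 2.5 to 4.0. Grades 2 to 4 cover lower counts only.
- **ALT and creatinine:** acceptable up to 60; Grade 1 starts at 1.1 × ULN.

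The table note and the List of Abbreviations both define ULN as the upper limit of normal. Neither defines a lower limit, and no numerical ULN is given for any test.

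The table is used in several places. Section 4.7 excludes children with "Laboratory screening tests out of range, specifically" those of Table 10. Section 5.6 treats the table as the normal range: "For all values outside the normal range (refer to Table 10), the reason and/or clinical condition will be documented". In the DSMB reports (Section 5.1.3.3), laboratory values are "presented as number of subjects out of range (above and below normal range) at each sampling time point" and "tabulated by toxicity grading scale (refer to Table 10"). For the final analysis, Section 10.8.1.2 says: "Frequency distribution of results by toxicity grades will be tabulated by group".

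**The concern.** A toxicity scale should give each value one status: acceptable, or one grade. The hemoglobin row does not. A grade meant to mark low hemoglobin is bounded above by an upper limit of normal, so ordinary acceptable values count as Grade 1 toxicity. The white-cell row has the same fault at its boundary.

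At stake is how the laboratory safety tables read. A child whose hemoglobin stays at 11 g/dL and a child who falls from 11 to 6.5 g/dL are both Grade 1 throughout. A Grade 1 count that includes both cannot show whether one vaccine group has more children with mildly low hemoglobin. Section 4.3 describes a setting where anemia is common, and the Synopsis describes this as the first study of RTS,S/AS01E in children, so the hemoglobin table should be readable.

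**Working it through.** The plan states no figure to reproduce. The check applies the table's limits to boundary values and notes the status of each.

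**Hemoglobin.** Grade 2 starts below 6.0, so Grade 1 runs from 6.0 up to, but not including, the ULN. The protocol gives no hemoglobin ULN, so 13, 14 and 15.5 g/dL were tried as assumptions. The results below are the same for all three.

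| Value (g/dL) | Acceptable (8.0 or more)? | Grade |
|---|---|---|
| 5.5 | no | 2 |
| 6.0 | no | 1 |
| 7.9 | no | 1 |
| 8.0 | yes | 1 |
| 10 | yes | 1 |
| 12.9 | yes | 1 |
| at the ULN | yes | none |

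The overlap is the whole interval from 8.0 to the ULN. Only a value at or above the ULN is acceptable and ungraded. Because Section 4.7 makes Table 10 the eligibility limit, every enrolled child with screening hemoglobin below the ULN is Grade 1 before any vaccine is given.

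**White cells (× 10³/µL).**

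| Value | Acceptable (4.0 to below 17)? | Grade |
|---|---|---|
| 3.9 | no | 1 |
| 4.0 | yes | 1 |
| 4.1 | yes | none |
| 16.9 | yes | none |
| 17 | no | none |
| 25 | no | none |

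The overlap is the single value 4.0. Counts of 17 or more are out of range and have no grade.

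**ALT and creatinine.** If ULN is taken as the table limit of 60 (an assumption), Grade 1 starts at 1.1 × 60 = 66, so whole-number values 61 to 65 are out of range with no grade. If the multiple is rounded to one decimal, half up, then 62/60 = 1.03 becomes 1.0 and 63/60 = 1.05 becomes 1.1, so only 61 and 62 remain ungraded. If ULN is instead a local value of 60/1.1 = 54.5 or lower, any value above 60 already exceeds 1.1 × ULN and the gap disappears.

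**The case against.** The strongest reply is that little depends on Grade 1. Hemoglobin Grades 2 to 4 are coherent as printed. The actions tied to grades start at Grade 3: the DSMB receives full clinical details from Grade 3 upward, and Section 8.6 says "All Grade 3, Grade 4 or clinically significant laboratory abnormalities will be followed up". The suspension criteria in Section 5.1.3.4 and the coprimary analyses use no laboratory grade. Out-of-range values are counted in the DSMB reports, documented and managed under Section 5.6, and described at Clinic Visit 6 under Section 10.8.1.2, so a fall below 8.0 g/dL still appears there. All of this stands, and it limits the point. It does not make the Grade 1 column correct, and no other section corrects it.

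A reader might infer more from the table, but three stronger readings are not supported:

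- **That high white-cell counts, and ALT or creatinine just above 60, are misclassified.** They are left ungraded, which is different, and they are still reported as out of range. Leaving high counts ungraded may be deliberate, since every white-cell grade runs downward. The ALT and creatinine gap depends on a ULN of 60. The protocol does not state that, and Appendix B has the investigator acquire local normal ranges.
- **That the trial could not detect a fall in hemoglobin.** Only Grade 1 is uninformative; Grades 2 to 4 and the out-of-range counts still work.
- **That the site's anemia figure measures how many trial children are affected.** Section 4.3 says "around 70% of children tested at HAS MRU have Hb < 9g/dL", but that describes children tested at the research unit. Enrolled children are healthy and need 8.0 g/dL or more at screening.

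**Conclusion.** The hemoglobin Grade 1 limit is wrong as written, and white-cell 4.0 is assigned twice. Both follow from the table alone and need no assumption about any ULN, beyond the hemoglobin ULN lying above 8.0 g/dL.

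The number of children affected cannot be given, because the hemoglobin ULN and the expected distribution of values are not stated. The ceiling is every child tabulated: the first 40 in each DSMB report and up to 180 at Clinic Visit 6, reached only if all have values from 6.0 g/dL up to the ULN. The white-cell overlap concerns one boundary value.

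Severity is low. The effect is confined to the Grade 1 entries of descriptive laboratory tables. That falls below 8.0 g/dL remain visible elsewhere assumes that the reference range in Section 10.8.1.2 is that of Table 10, as Section 5.6 treats it. The ALT, creatinine and high white-cell entries call for clarification only.

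**What to change.** Correct two cells of Table 10 before the first DSMB report:

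- **Hemoglobin Grade 1:** 6.0 to below 8.0 g/dL, which matches the table's own acceptable limit.
- **White-cell Grade 1:** 2.5 to below 4.0 × 10³/µL.

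The sponsor should confirm the hemoglobin limit. A stated lower limit of normal would be an alternative if grading above 8.0 g/dL is wanted, because under the limit proposed here a fall from 11 to 8.5 g/dL would be ungraded.

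Two table notes would complete the correction. The first states whether ULN for ALT and creatinine is the Table 10 limit of 60 and, if so, starts Grade 1 at more than 1.0 × ULN. The second says that white-cell counts of 17 or more are reported as above range and not graded.

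The cost is one corrected table. Eligibility limits, visits, blood volumes and data collection do not change.
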